#### 10.1.2 Attack rate per dose group

The attack rate will be calculated by division of the number of volunteers with female *Sm* infection by the total number of volunteers in the per protocol analysis, multiplied by 100% (e.g. POS/TOTAL subjects \* 100%). Volunteers withdrawing from the trial procedures at any time after infection and before the end of the study, will be tabulated as positive and included in the per protocol analysis if they had a serum CAA  $\geq 1$  pg/mL at any timepoint after exposure and before praziquantel treatment. They will be excluded from the analysis if there was no positive serum CAA sample until the moment of withdrawal.

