### 5.3 Escape medication

The trial physician may decide to abrogate the study for individual subjects according to the criteria described in section 8.4. Because early treatment of schistosomiasis infection has been shown to aggravate clinical symptoms in reported cases, the advantages and disadvantages of such escape medication should be carefully weighed. Escape medication should, in symptomatic cases, be accompanied by symptomatic treatment with corticosteroids.

Escape medication to abrogate the study for individual volunteers before week 8 of the study will be artemether/lumefantrine in a standard 6-dose treatment regimen over 3 days. Volunteers with early abrogation of infection are also treated with praziquantel 60 mg/kg at week 8.

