### **Follow-up after infection**

Volunteers will visit the trial centre for screening, then at the day of infection and every week starting from 1 week after infection until 16 weeks after infection. After week 16, biweekly follow-ups will follow until week 20. Final visit will be performed at 1 year after infection. At all follow up visits, adverse events will be recorded, volunteers will undergo a blood draw by venepuncture and will provide a urine sample. At every visit the tympanic temperature will be checked (until week 12). A focused physical examination will be performed if deemed necessary by the trial physician. Volunteers are requested to keep a diary from the day of infection until 20 weeks, in which they record adverse events. A clinical trial physician will be available by mobile phone 24/7 during the 20 weeks clinical trial period. Volunteers will be instructed to report to the clinical trial physician in case of any grade 2 (moderate) or grade 3 (severe) adverse events to ensure early detection and possible treatment of symptoms of acute Schistosomiasis infection (see paragraph 9.2.4 [Adverse events data collection](#) for more detailed information).

Additional diagnostics (including serum CAA tests) can be performed on discretion of the trial physician at any time if it is deemed necessary for the safety of the study volunteers.

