#### **8.4 Withdrawal of individual subjects**

Subjects can leave the study at any time for any reason if they wish to do so without any consequences. However, for safety purposes volunteers will be required to complete some follow-up visits to monitor treatment. The investigator can decide to withdraw a subject from the study for urgent medical reasons.

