#### **8.6 Follow-up of subjects withdrawn from treatment**

If a subject fails to appear for a follow-up examination, extensive effort (i.e. documented phone calls and certified mail) will be undertaken to locate or recall him or at least to determine his health status. These efforts will be documented in the source documents. In the event that a volunteer discontinues the study for any reason, he/she will be urged to complete all safety follow-up, including treatment with praziquantel.

Figure 3. Flow chart

|                                              | Screening        | Challenge      | Follow up |    |    |    |    |    |    |                |     |     |     |     |     |     |     |     |     |     |         |  |
|----------------------------------------------|------------------|----------------|-----------|----|----|----|----|----|----|----------------|-----|-----|-----|-----|-----|-----|-----|-----|-----|-----|---------|--|
| Deviation                                    |                  |                | 3 days    |    |    |    |    |    |    |                |     |     |     |     |     |     |     |     |     |     | 4 weeks |  |
| Visit                                        |                  | V1             | V2        | V3 | V4 | V5 | V6 | V7 | V8 | V9             | V10 | V11 | V12 | V13 | V14 | V15 | V16 | V17 | V18 | V19 | V20     |  |
| Week                                         |                  | 0              | 1         | 2  | 3  | 4  | 5  | 6  | 7  | 8              | 9   | 10  | 11  | 12  | 13  | 14  | 15  | 16  | 18  | 20  | 52      |  |
|                                              |                  |                |           |    |    |    |    |    |    |                |     |     |     |     |     |     |     |     |     |     |         |  |
| Obtain informed consent                      | X                |                |           |    |    |    |    |    |    |                |     |     |     |     |     |     |     |     |     |     |         |  |
| Clinical evaluation                          | X                | X              | X         | X  | X  | X  | X  | X  | X  | X              | X   | X   | X   | X   | X   | X   | X   | X   | X   | X   | X       |  |
| Exposure to cercariae                        |                  | X              |           |    |    |    |    |    |    |                |     |     |     |     |     |     |     |     |     |     |         |  |

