#### j. Can effects be managed?

In case treatment would be required for dermatitis, triamcinolone cream 0.5% can be applied according to local clinical practice [13]. Acute schistosomiasis syndrome may be treated symptomatically with analgesics, non-steroidal anti-inflammatory drugs or corticoids [6, 21, 26]. The parasite load may be effectively reduced by over 90% after a single dose of 40 mg/kg praziquantel [6]. In our study, we treat the volunteers with two rounds of praziquantel 60 mg/kg at week 8 and week 12. The first dose is timed just after maturation of the larvae to further reduce any risk of egg accumulation. Some data suggests that the EC50 for single-sex female infection both in vivo (rodent) and in vitro [18] are higher than for mixed-sex infection indicating that a 60 mg/kg dose may be more appropriate. Validated sensitivity tests for *Schistosoma mansoni* are not available, but there is no firm clinical or epidemiological evidence for the emergence of praziquantel resistance in the field [21, 22, 30]. As an alternative to praziquantel, which is only active on the mature *Schistosoma* worm (~7 weeks post infection) [18, 22], artemisinin derivatives may be used to abrogate early infections [31]).

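### Section 10.1.2 cuts off withdrawn volunteers' CAA results at two different points, and its exclusion rule drops known negatives while keeping positives

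*Protocol*

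**What the plan says.** Section 10.1.2 defines the attack rate as "division of the number of volunteers with female *Sm* infection by the total number of volunteers in the per protocol analysis", times 100%. It then covers volunteers who withdraw from trial procedures after infection and before the study ends, in two sentences:

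- Inclusion: counted as positive if serum CAA was at least 1 pg/mL "at any timepoint after exposure and before praziquantel treatment".
- Exclusion: "They will be excluded from the analysis if there was no positive serum CAA sample until the moment of withdrawal".

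Other sections bear on what is known about such a volunteer:

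- Section 8.4: "However, for safety purposes volunteers will be required to complete some follow-up visits to monitor treatment".
- Section 8.6, for anyone who discontinues: "he/she will be urged to complete all safety follow-up, including treatment with praziquantel".
- Section 8.3 (follow-up after infection): "At all follow up visits, adverse events will be recorded, volunteers will undergo a blood draw by venepuncture". Figure 3 has serum CAA at every visit, week 8 included.
- Section 8.3 (safety laboratory evaluation): successful infection is assessed by serum CAA at week 8.
- Section 5.3: "Volunteers with early abrogation of infection are also treated with praziquantel 60 mg/kg at week 8".
- Section 12.1: if consent is withdrawn, data and samples collected up to then may be analysed.
- Section 3: follow-up runs to one year.

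**The concern.** The two sentences use different end points, and this does two separate kinds of harm.

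(a) Contradiction. A volunteer who leaves while CAA-negative and turns positive before praziquantel is infected under the inclusion sentence and absent under the exclusion sentence.

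(b) Selective exclusion. The exclusion sentence looks only at whether a positive sample exists, not at whether the outcome is known. Praziquantel is first given at week 8, but withdrawal can happen up to week 52. Someone negative at every sample through week 8 who leaves at, say, week 15 has a complete infection outcome and is still removed. A positive volunteer leaving on the same day stays in. Removal therefore depends on the outcome and can only push the rate up or leave it unchanged.

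The attack rate is part of the primary objective. The main endpoint in section 8.1.1 is the dose at which 100% of volunteers are CAA-positive, and section 4.4 aims for 100% in 10 subjects. With groups of 3 and 10, one volunteer matters.

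**Working it through.** **Yardstick.** The disputed sentences carry no figure. The nearest is in section 4.4: precision of about ±22.5 points at 80% with n = 10. A Wilson 95% interval for 8/10 runs from 49.0% to 94.3%, a half-width of 22.7 points, so that figure is reproduced and is not in dispute.

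**Assumption.** The protocol gives no withdrawal rate, so each case takes one affected volunteer.

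**Case (a): first positive between withdrawal and praziquantel.** Let n be the group size and k the positives among the other n − 1. The inclusion sentence gives (k+1)/n and the exclusion sentence gives k/(n−1). The difference is (n−1−k)/[n(n−1)].

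| n | k | Included | Excluded | Difference (points) |
|---|---|---|---|---|
| 3 | 0 | 1/3 = 33.3% | 0/2 = 0% | 33.3 |
| 3 | 1 | 2/3 = 66.7% | 1/2 = 50.0% | 16.7 |
| 3 | 2 | 3/3 = 100% | 2/2 = 100% | 0 |
| 10 | 7 | 8/10 = 80.0% | 7/9 = 77.8% | 2.2 |
| 10 | 8 | 9/10 = 90.0% | 8/9 = 88.9% | 1.1 |
| 10 | 9 | 10/10 = 100% | 9/9 = 100% | 0 |

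The disputed volunteer is either positive or excluded, never negative. Hence (k+1)/n = 1 exactly when k/(n−1) = 1, and a rule that asks whether fewer than 100% are infected gives the same answer under both sentences.

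**Case (b): negative through week 8, withdrawn later.** With p positives among n, the rate on known outcomes is p/n and the rule as written gives p/(n−1). The excess is p/[n(n−1)].

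| n | p | Known outcomes | As written | Excess (points) |
|---|---|---|---|---|
| 3 | 1 | 1/3 = 33.3% | 1/2 = 50.0% | 16.7 |
| 3 | 2 | 2/3 = 66.7% | 2/2 = 100% | 33.3 |
| 10 | 8 | 8/10 = 80.0% | 8/9 = 88.9% | 8.9 |
| 10 | 9 | 9/10 = 90.0% | 9/9 = 100% | 10.0 |

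The exact (Clopper-Pearson) lower 95% limit moves from 55.5% (9/10) to 66.4% (9/9), and from 44.4% (8/10) to 51.8% (8/9). The second shift crosses the 50% mark that section 4.4 uses.

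**Replacement.** Under section 8.5, a withdrawal from group A raises group B to 8, so the full dose group is 11 exposed. Case (a) with k = 7 is then 8/11 = 72.7% against 7/10 = 70.0%. Case (b) with 10 positives is 10/11 = 90.9% against 10/10 = 100%. The tables for n = 10 describe a withdrawal from group B.

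**The case against.** **The sentences can be read together.** Praziquantel would be the limit for those who leave after week 8 and withdrawal the limit for those who leave before, so the window closes at whichever comes first. That is a sensible intention, but the inclusion sentence names its own end point and does not say this. The reading would also leave case (b) untouched.

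**Case (a) is narrow.** This stands. Section 12.1 settles it for withdrawn consent. A volunteer whose infection is abrogated early receives artemether/lumefantrine, which section 11.3 describes as active on immature stages, so later conversion is less likely. The visits in section 8.4 are for monitoring treatment and could all follow praziquantel, and section 8.6 only urges attendance. Figure 3 lists serum CAA separately from the safety tests. Samples between withdrawal and praziquantel are therefore possible, not assured. Section 13.1 j puts worm maturity at about 7 weeks, from which a reader might infer that early leavers are typically still negative. The protocol gives no time to CAA positivity, so that does not follow.

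**The dose decisions.** A reader might infer that escalation depends on which sentence is applied. The documents do not support that in general: sections 3 and 9.5 rest on detectable serum CAA and do not cite 10.1.2 or its per protocol set. If 10.1.2 were imported, case (a) could not change the under-100% rule. It could matter only in group A at 60 cercariae with the disputed volunteer as sole positive (1/3 would open group B, 0/2 would not), or if the requirement that all three be positive is taken as a head count. In case (b), importing 10.1.2 would make 2/3 read as 2/2 if the volunteer left before the week-10 decision, but nothing in the protocol says it is imported.

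**This belongs in the SAP.** An SAP may refine withdrawal handling. Here the protocol already fixes the rule, and fixes it inconsistently.

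**Conclusion.** The point holds for the reported attack rate. The two cut-offs conflict for a first positive between withdrawal and praziquantel. That case is uncommon, costs 16.7 to 33.3 points in a trio when another member is negative, and only 2.2 points at 8/10, small beside the planned ±22.5.

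The larger fault is the exclusion of known negatives. One such volunteer adds 8.9 to 10.0 points in a group of 10 with 8 or 9 positives, always upward, and can turn a missed 100% target into an apparent success. Section 12.1 does not cure this: even after withdrawal of consent it allows the week-8 result to be used, while 10.1.2 discards it.

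These sizes assume one affected volunteer per group and literal application of 10.1.2. No general effect on dose escalation is established.

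**What to change.** Replace the exclusion sentence in 10.1.2, and give the inclusion sentence the same end point, so that:

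- a withdrawn volunteer is scored on all available serum CAA samples taken after exposure and before the first antischistosomal treatment, up to withdrawal of consent where section 12.1 applies;
- the volunteer is positive if any of these is at least 1 pg/mL;
- the volunteer is negative if all are negative and the week-8 pre-treatment sample is available;
- the volunteer is excluded only if there is no positive sample and no week-8 pre-treatment sample.

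Ending the window at the first antischistosomal treatment, not at praziquantel, also settles samples taken after escape medication. This concerns scoring only and changes no treatment.

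State that the dose decisions in sections 3 and 9.5 use the same scoring, and name serum CAA in section 8.6 among the pre-praziquantel assessments for volunteers who have discontinued.

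The cost is a few sentences of text. Figure 3 already schedules the samples, so no visit or sampling time point is added.

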### 10.2 Other study parameters

Delays in the time to positive serum or urine CAA test will be examined using Kaplan-Meier plot and log-rank (Mantel Cox) test, whereby different dose groups or a historical comparison with the male *Sm* cercariae infection will be made.

In the exploratory immunological analyses we will assess differences by comparing mean values between the dose groups or the infected/uninfected individuals using either a two-tailed student's t-test or non-parametric equivalents, paired if pre-infection values are compared with post-infection values, unpaired if comparisons are made between independent groups. For categorical variables (e.g. the number of positive assays), the chi-squared test or Fisher's exact test will be used (two-tailed). Similar to the CAA kinetics, historical comparison with the male *Sm* cercariae infection will be made.

To compare the metabolic changes after infection targeted metabolomics and changes in the microbiome, a straightforward multivariate analysis with a more general screen and multivariate modeling with principal component analysis (PCA) and partial least square

(PLS) analysis will be used. Also specific approaches for the time-resolved analysis will be used, multilevel analysis and/or (ANOVA)-simultaneous component analysis (ASCA).

## 11. ETHICAL CONSIDERATIONS

### 11.1 Regulation statement

The study will be conducted according to the principles of the Declaration of Helsinki (amended by 64th WMA assembly, Fortaleza, Brazil, published JAMA November 27, 2013 Volume 310, Number 20) and in accordance with the Medical Research Involving Human Subjects Act (WMO)

### 11.2 Recruitment and consent

Following approval by the accredited METC, advertisements will be placed in prominent places in public places as well as social media, on the website of the LUMC department of parasitology and infectious diseases and [www.vaccinonderzoek.nl](http://www.vaccinonderzoek.nl). Furthermore, a Facebook page showing the advertisement text will be designed to inform people about the trial and advertisements will be placed on local student websites.

The investigators will be responsible for providing adequate verbal and written information regarding the objectives and procedures of the study, the potential risks involved and the obligations of the volunteers. Volunteers will be informed that they will not gain health benefits from this study. Trainees or other students who might be dependent on the investigators or the study group will not be included in the study. After free discussion with the investigator, the volunteer will be given sufficient time, at least 72 hours, to consider participation. During the screening visit written informed consent is obtained from the volunteer. A sample volunteer information letter containing this information and informed consent form can be found in Sections E1 and E2.

Volunteers will be informed that they can withdraw their informed consent at any time during the study.

### 11.3 Benefits and risks assessment, group relatedness

There is no benefit of participation in the trial for the individual volunteer. Therefore the risk and discomfort of participation for individual volunteers should be carefully weighed against the scientific advantage of the controlled human *Schistosoma mansoni* infection model, in particular for vaccine and drug development. The CoHSI model has the potential to be extremely instrumental to vaccine and drug discovery and clinical testing for the widespread disease of *Schistosoma mansoni*, with an enormous global disease burden, and as such may have unprecedented repercussion for public health. Moreover,

the development of a female-only controlled human *Sm* infection model in addition to the previously established male-only model will allow further exploration of sex-specific immune responses.

The risks associated with participation in this study are related to infection with female helminths from the species *Schistosoma mansoni*. Several aspects should be considered in the risk assessment:

1. Risks of infection with female *Schistosoma mansoni*

Please refer to section 2.3.2 of the Product Dossier for a description of the clinical experience with *Schistosoma mansoni* infections in travelers and the male controlled human *Schistosoma mansoni* infection.

In summary, three main complications could occur following infection with female *Schistosoma mansoni* cercariae:

a. Swimmer's itch

A discrete urticarial rash at the site of entry of cercariae. The chances of this complication occurring is very likely, however, we expect the rash to be very mild as the number of cercariae penetrating the skin is low. In the CoHSI1 study 16 out of 17 volunteers reported a mild rash at the site of infection. All these rashes started within two days after the exposure and severity peaked one week after infection. None of the rashes required treatment. In case severe discomfort occurs, the urticarial rash can be treated with local triamcinolone cream 0.5%.

b. Acute schistosomiasis syndrome

A flu-like syndrome with protracted low to medium grade fever, fatigue, myalgia, malaise, non-productive cough, eosinophilia and patchy infiltrates on chest radiography can occur. Because it is unclear whether an acute schistosomiasis syndrome is related to the number of infected schistosomes or oviposition, it is hard to predict the chances of Katayama fever occurring and in which dose group. In the CoHSI1 study, two volunteers (out of three) in the 30 cercariae dose group developed symptoms of an acute schistosomiasis syndrome [11] that resolved without treatment. Another two (out of 11) in the 20 cercariae dose group developed severe AEs suggestive acute schistosomiasis syndrome [11]. In severe cases the syndrome can be treated symptomatically with analgesics, NSAIDs and corticosteroids.

c. Morbidity related to oviposition

Eggs trapped in the intestines or liver can induce a granulomatous host immune response that may present as abdominal pain, diarrhoea, and rectal

bleeding. The frequency of these symptoms is positively associated with the infection intensity. In severe cases, chronic inflammation may lead to periportal fibrosis resulting in clinical symptoms observed in individuals with portal hypertension, such as hepatomegaly, ascites, or oesophageal varices. The time between initial infection and these advanced stages are approximately 5-15 years [19]. In contrast to the male-only infections where egg production was never reported, we and others have in rare occasions observed egg-production in single-sex female infection of mice [20]. The numbers of eggs recovered were substantially lower as compared to mixed infections (please also see paragraph 13.1) and were never found to contain a viable miracidium. Possibly, the single female can produce and secrete egg shells on rare occasions. To reduce the possible production and number of egg(shells) we have adjusted the dose schedule to as low as possible doses of female cercariae and will initiate treatment as soon as the worm reaches adulthood and is possibly capable of producing eggs.

d. Acute toxemic neuroschistosomiasis

Neurological symptoms, such as low back pain irradiating to the limbs, lower limb muscle weakness, paresthesia, acute encephalitis, encephalomyelitis, aseptic meningitis are rare complications of schistosomiasis and thought to occur as a consequence of an inflammatory response of the host against the *Schistosoma* eggs deposited in the central nervous system by ectopic worms. Given the fact that this complication, even in endemic areas where worm burden is high, is rare, it is highly unlikely to happen after infection with female *Schistosoma mansoni* only.

2. Risks related to treatment with praziquantel

Please refer to section 2.3.2.2. of the Product Dossier for an extensive description of the available treatment options. In summary, praziquantel is the only registered, extremely safe and highly effective drug for the treatment of *Schistosoma mansoni* infections. Because it is active on the mature worms only, treatment is recommended from 2-3 months after infection. Praziquantel is extremely safe with no long-term toxicity also for infants and pregnant women [6, 21, 22]. The short-term side effects are primarily fatigue, malaise, gastro-intestinal side effects and dizziness (see SPC Praziquantel) which are directly correlated with the pre-treatment intensity of infection [22]. Because of the risk of dizziness, volunteers are advised not to drive a car or operate machinery for the day of treatment and the day thereafter. In very rare instances, allergic reactions have been reported [22].

